## Results

The WE2CARE study protocol has been approved by the research ethics boards of Ryerson University (REB 2019-036) and the University of Toronto (RIS37623). Data collection occurred between November 2019 and May 2020. Of 18 participants in the intervention group, one did not complete the baseline questionnaire, while 6 of 18 participants in the control group withdrew from the study due to other competing life priorities. The total number of participants who completed the study was 29, with 17 in the intervention group and 12 in the control group. Our intervention group was divided into two cohorts of 9 and 8 participants, respectively. This allowed more opportunity for participants to share their experiences, mental health stressors, and application of ACT strategies during weekly videoconferences. The control group received the intervention after the two intervention cohorts were completed. Data analysis is in progress and results will be published in 2021.

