**Results:**

WE2CARE was funded in January 2019 for a year. The protocol was approved by the research ethics boards of Ryerson University (REB 2019-036) and the University of Toronto (RIS37623) in February and May 2019, respectively. Data collection started upon ethics approval and was completed by May 2020. A total of 29 caregivers completed the study and 20 participated in the focus groups. Data analyses are in progress and results will be published in 2021.

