### Participants and Recruitment Strategies

A total of 36 participants will be recruited by two community champions (ie, trusted members of the caregivers’ community collaborating with community health organizations serving the TFW population) and a snowball sampling technique. The inclusion criteria will include the following: (1) female adults aged ≥18 years, (2) residing in the Greater Toronto Area, (3) working on a temporary work permit as live-in caregivers, (4) able to speak and read English, (5) have internet access, and (6) able to take part in the 6-week intervention. They will be randomized to either the intervention arm or control arm using a random number generator.

In Phase 2 of our study, we will conduct two focus groups with a subset of participants from Phase 1 who indicate interest in participating. The aim of the focus groups is to gain a deeper understanding about participants’ views of the effectiveness of WE2CARE in promoting mental health, their perceived barriers and challenges in accessing this method of delivery (ie, online), and their recommendations to improve the content and method of delivery of this program.

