### Data Collection

Informed consent will be obtained prior to data collection. Data will be gathered using both quantitative and qualitative tools, which include self-completed questionnaires and focus groups.

Quantitative data will be captured for participants in the control and intervention groups through self-report instruments that will be administered online pre- and postintervention. The intervention group will also complete the questionnaires 6 weeks postintervention. The survey questionnaires will include the following:

1. The preintervention survey will include sociodemographic and health-related questions.

2. The standardized scales administered preintervention, postintervention, and at the 6-week follow-up will include the following:

The Depression, Anxiety and Stress Scale (DASS-21), a set of three self-report scales (21 items) designed to measure the emotional states of depression, anxiety, and stress.The Acceptance and Action Questionnaire (AAQ-2), a 7-item scale specifically designed to measure the impact of ACT core processes conceptualized as psychological flexibility.The Cognitive and Affective Mindfulness Scale – Revised (CAMS-R), a 12-item measure designed to capture a broad conceptualization of mindfulness not specific to any particular type of meditation training.The Multi-System Model of Resilience Inventory (MSMR-I), which consists of three subscales: internal resilience, pursuits and coping, and external resilience. Each subscale contains 9 self-reported items and indicates where the barriers to one’s resilience lie. These scales have shown good psychometric properties including internal consistency, test-retest reliability, and validity.

3. Participants’ evaluation of the WE2CARE program. Participants’ feedback about the program will be captured through a 12-item questionnaire that elicited their perceptions of the impact the program had on their mental and social well-being and their knowledge of how to access mental health services.

Qualitative data will be obtained through focus groups and interactive entries embedded throughout the 6 online modules, including questions on caregiving burden and factors that promote resilience in Module 1 and weekly valued action data logs on self-care in Modules 2-6.

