### Data Analysis Planning

Descriptive statistics will be used to summarize participants’ sociodemographics, self-reported health characteristics, and practices. Both independent and dependent *t* tests will be performed to assess the mean score differences for each outcome measure across and within groups. An independent *t* test will be used to compare mean scores across the intervention and control groups. Paired *t* tests will be used to compare the following: (1) baseline and postintervention outcomes and (2) baseline and 6-week postintervention outcomes among intervention participants.

The number of intervention participants at low risk and at risk for anxiety, depression, and stress will also be compared at baseline, postintervention, and 6 weeks postintervention. The Fisher exact test will be used to determine if the number of intervention participants at risk for anxiety, depression, and stress changed across time. Risk for anxiety, depression, and stress will be assessed using the DASS-21 and AAQ-7. The DASS-21 contains three subscales that assess anxiety, depression, and stress. Those that score at a moderate severity level or above for anxiety, depression, and stress will be considered at risk. The cutoffs for a moderate severity level will be set at 9 for anxiety, 13 for depression, and 18 for stress. Based on the AAQ-7 scoring instructions, a score above 23 is associated with depression or anxiety symptoms.

Linear mixed effects models will be created for each outcome of interest from baseline to postintervention among participants in the intervention and control groups. Each model will include two fixed effects parameters and two random effects parameters, one for the intercept and one for the outcome. The intercept fixed effect represents the typical initial score of an outcome and the outcome fixed effect represents the typical increase or decrease in score from baseline to postintervention.

Participants’ feedback on the 12-item questionnaire will be stratified by study arm allocation and an independent *t* test will be used to determine if there are differences in survey responses by study arm allocation.

Quantitative data will be analyzed using SPSS (version 27; IBM Corp) and R (version 1.2.5003; R Foundation for Statistical Computing) for Windows. A threshold of .05 will be used to determine the level of significance for all *P* values.

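### The within-arm tests, above all the uncontrolled baseline-to-6-week comparison, cannot separate a calendar-time shift in distress from programme change

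*Protocol article*

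**What the plan says.** All references are to the protocol article.

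- **Window.** The Results section says "Data collection occurred between November 2019 and May 2020". The Abstract (Results) says "Data collection started upon ethics approval and was completed by May 2020", having placed the two ethics approvals in February and May 2019.
- **Delivery.** In the Results section, "Our intervention group was divided into two cohorts of 9 and 8 participants, respectively" and "The control group received the intervention after the two intervention cohorts were completed". No cohort dates are given, and nothing says whether the cohorts ran together or in turn.
- **Measurement.** In Data Collection, "Quantitative data will be captured for participants in the control and intervention groups through self-report instruments that will be administered online pre- and postintervention". Only the intervention arm answers again 6 weeks later.
- **Analysis.** Data Analysis Planning sets an independent t test between arms. It adds paired t tests, one of which compares "baseline and 6-week postintervention outcomes among intervention participants", and a Fisher exact test of whether at-risk counts in the intervention arm change over time. The linear mixed models run from baseline to postintervention and have two fixed effects, an intercept and a change. As described they contain no term for arm, cohort or date.

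**The concern.** The outcomes are depression, anxiety, stress, psychological flexibility, mindfulness and resilience, all self-reported and all able to move with outside circumstances. Collection stretched over roughly half a year and ended in May 2020. A before-and-after test in one arm attributes all change between two visits to the programme. If conditions for the whole population changed between those visits, that change is counted too.

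The postintervention visit at least has a randomised control arm. The 6-week visit has none, and it also holds the latest intervention-arm questionnaires. A rise in distress would hide a real benefit there or look like harm, and a fall would look like a lasting benefit. Either would mislead a pilot whose stated use is to guide adoption of the intervention.

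**Working it through.** **1. Counts in the Results section.** Intervention: 18 − 1 = 17. Control: 18 − 6 = 12. Total: 17 + 12 = 29. Cohorts: 9 + 8 = 17. These reproduce the stated completers: "The total number of participants who completed the study was 29, with 17 in the intervention group and 12 in the control group".

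**2. Assumptions not in the documents.** A shift in distress of s SD takes effect about mid-March 2020, when pandemic restrictions are assumed to have begun. Its size and direction are unknown, so a range is shown.

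**3. Bias in the within-arm 6-week change.** Bias = (share of the 17 whose 6-week questionnaire falls after the date, with baseline before it) × s.

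| Follow-up after the date | Share | s = 0.2 | s = 0.4 | s = 0.6 |
|---|---|---|---|---|
| None | 0 | 0 | 0 | 0 |
| Cohort of 8 only | 8/17 = 0.471 | 0.09 | 0.19 | 0.28 |
| Cohort of 9 only | 9/17 = 0.529 | 0.11 | 0.21 | 0.32 |
| All | 1 | 0.2 | 0.4 | 0.6 |

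**4. Effect on error rates.** A simulation with no programme effect was run (20,000 runs per scenario, nominal level 0.05, assumed pre/post correlation 0.5, with 0.7 in brackets). The entries are false-positive rates.

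| Scenario | s = 0.3 | s = 0.5 | s = 0.8 |
|---|---|---|---|
| Paired t, n = 17, all follow-up shifted | 0.22 (0.32) | 0.49 (0.71) | 0.87 (0.98) |
| Paired t, cohort of 8 shifted | 0.08 (0.10) | 0.14 (0.19) | 0.26 (0.37) |
| Pooled change, n = 29, all post visits shifted | 0.35 (0.52) | 0.74 (0.92) | 0.99 (1.00) |
| Between-arm t, 17 v 12, all post visits shifted in both arms | 0.05 | 0.05 | 0.05 |

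The third row stands in for the two-parameter mixed model. In the fourth row the bias is about zero: a shift shared by both arms cancels.

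**5. When the between-arm test would be affected.** Suppose only the cohort of 8 is shifted.

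- Controls spread over the same dates: bias about −0.01 to −0.02 SD for s from 0.3 to 0.8, with error rates of 0.03 to 0.05.
- Controls all before the shift: bias about (8/17)s, or 0.14 to 0.38 SD.
- Controls all after it: bias about −(9/17)s, or −0.16 to −0.42 SD.

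In the last two cases the error rate is 0.06 to 0.17.

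**6. Calendar check.** The stated window is about 22 weeks (30 November to 1 May) to 30 weeks (1 November to 31 May). Take a first baseline between 1 and 30 November 2019 and no gap between cohorts.

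- Concurrent cohorts: last 6-week visit after 6 + 6 = 12 weeks, 24 January to 22 February. All precede mid-March.
- Cohorts in turn: last postintervention visit after 6 + 6 = 12 weeks, again 24 January to 22 February. Last 6-week visit after 18 weeks, 6 March to 4 April.

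Both schedules fit the window, so the article does not settle which was used. With cohorts in turn, the 6-week visit can straddle mid-March. The postintervention visit reaches it only with an added delay of roughly 3 to 7 weeks.

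**The case against.** The strongest case against is that no passage mentions an event or a change in distress in spring 2020. The shift, its date and its direction are supplied from outside, and every bias figure is an assumed s times a fraction. This stands as a limit on the size of the point. It does not touch the structural part: a one-arm before-and-after test cannot separate time from treatment, whatever the cause of the time trend.

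Second, allocation is random ("They will be randomized to either the intervention arm or control arm using a random number generator") and a between-arm t test is planned. A reader might infer that the whole estimated programme effect is confounded with calendar time. The article does not support that, because a shared shift cancels when the arms answer over the same dates. A reader might also infer that one control post-test cannot match two cohorts in time. But one post-test per person is not one date for the whole arm, and the article gives no control dates. The cohort split is explained by opportunity for discussion in the videoconferences, so running the cohorts in turn is an inference too. The May 2020 end may reflect the control arm's later programme rather than intervention-arm scores.

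Third, a date or cohort covariate could sit in an analysis plan not shown. That is right, and its absence is not the complaint. The point rests on what the article does fix: uncontrolled within-arm tests and a model with two fixed effects.

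Finally, the two start dates are only a matter of wording here. An earlier start would not by itself move any questionnaire past mid-March.

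**Conclusion.** The point holds for the within-arm analyses and for the mixed model as described, and most clearly for the 6-week change, which has no control value. These analyses would report any time trend within the window as programme change. The size is conditional. Under the assumed mid-March shift, the 6-week bias runs from zero to s, and is 0.47s to 0.53s if one cohort is affected. For s of 0.2 to 0.6 SD, the one-cohort case is 0.09 to 0.32 SD.

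The point does not extend to the randomised postintervention comparison unless completion dates differ by arm, which is unknown. If the cohorts ran back to back from November, all postintervention questionnaires would precede mid-March. Confidence that any bias actually occurred is low, and completion dates would show whether the exposure existed.

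**What to change.** 1. Tabulate completion dates by arm, cohort and time point, marking those before and after the assumed date.
2. Rest the effectiveness conclusion on the concurrent between-arm postintervention comparison, and present within-arm changes as descriptive.
3. If any 6-week questionnaires fall after the date, report 6-week scores separately before and after it, and do not interpret the pooled 6-week change as a programme effect.
4. Repeat the between-arm comparison on questionnaires from before the date only if the table shows that the arms differ in dates.
5. Reconcile the start of data collection between the Abstract and the Results section.

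The cost is one table and, at most, two small additional analyses. They use completion dates that online survey systems normally hold, and the article says analysis is still under way. The downside is precision: splitting 17 participants may leave groups of about 9 and 8, and a restricted between-arm comparison would start from only 17 against 12.

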### Treatment Intervention

#### Overview

The WE2CARE intervention consist of six e-learning modules that cover the ACT processes. Each week, participants are invited to complete an online, self-directed, interactive experiential session on ACT strategies (approximately one hour to complete) and to attend a 90-minute live online videoconference during which group discussions and question-and-answer sessions are facilitated by our research team members to support participants’ ACT practice.

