#### Module 6: Committing to Valued Action

This module supports participants to consolidate their commitment to self-care by doing the following: (1) developing concrete short, intermediate, and long-term plans for self-care and (2) anticipating future barriers and formulating mitigating ACT strategies to sustain a commitment to self-care (committed action, values, present moment).

One of the therapeutic goals of WE2CARE is to motivate participants to engage collectively in building social support networks. The weekly videoconference, which will be cofacilitated by two trained research team members, will provide a viable venue to facilitate and model the development of a virtual community of mutual support, which may continue beyond the project.

A previous ACT intervention study conducted by our team members demonstrated that a participant-driven social support e-network (a closed group on Facebook) was effective in reducing social isolation, promoting community engagement, and strengthening mutual support.

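### The intervention was delivered in two interactive groups, but no planned analysis allows for correlation within a group; if outcomes correlate, standard errors involving that arm are too small

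*Protocol article*

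**What the plan says.** All references are to the protocol article.

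- **Allocation.** Under Participants and Recruitment Strategies the unit is the individual woman: "They will be randomized to either the intervention arm or control arm using a random number generator".
- **Delivery.** The Overview of the Treatment Intervention pairs a self-directed weekly module with a group session. Participants are invited to "attend a 90-minute live online videoconference during which group discussions and question-and-answer sessions are facilitated by our research team members". The text under Module 6 makes interaction part of the treatment: "One of the therapeutic goals of WE2CARE is to motivate participants to engage collectively in building social support networks".
- **Grouping.** Results reports: "Our intervention group was divided into two cohorts of 9 and 8 participants, respectively". The stated reason is to give women more room to share during the sessions.
- **Controls.** Also in Results: "The control group received the intervention after the two intervention cohorts were completed". No group activity is described for them at the post-test.
- **Numbers.** Completers are reported as 29, "with 17 in the intervention group and 12 in the control group".
- **Analysis.** Data Analysis Planning lists "Both independent and dependent" t tests, a Fisher exact test of risk status over time in the intervention arm, and linear mixed models. Each mixed model has two fixed and two random effects, described as initial score and change. No cohort term appears, and every P value is read against .05.

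**The concern.** This is a partially nested design: individual randomisation, with grouping after randomisation in one arm only. Women who spend six weekly 90-minute sessions in the same group, with peer support as an intended mechanism, may end with outcomes more alike than those of women in different groups. The variance of the intervention mean then contains a between-cohort part that tests assuming 17 independent women do not see. Confidence intervals come out too narrow and P values too small.

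The paired tests are the more exposed, because the between-arm comparison is diluted by an unclustered control arm and the paired tests are not. They also matter to the plan. Data Collection gives the 6-week questionnaires to the intervention group only, so the paired tests are the only mean-score comparison planned at that time point.

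**Working it through.** **Inputs from the article.** Cohorts of 9 and 8; 17 intervention and 12 control completers; threshold .05. The counts agree: 18 − 1 = 17, 18 − 6 = 12, 17 + 12 = 29, 9 + 8 = 17. The target of 36 has no stated derivation, so there is no planned figure to reproduce.

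**Assumptions.** No ICC is given; the range 0 to 0.20 is assumed. Tests are taken as two-sided, with equal total variance in the two arms and no clustering among waiting controls.

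**Step 1: design effect in the intervention arm.** The size-weighted mean cohort size is (9² + 8²)/17 = (81 + 64)/17 = 8.53. So DE = 1 + (8.53 − 1) × ICC = 1 + 7.53 × ICC.

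**Step 2: standard error of the between-arm difference.** True SE relative to the SE under independence = sqrt((DE/17 + 1/12)/(1/17 + 1/12)). At ICC 0.05, DE = 1.376, and the ratio is sqrt((0.0810 + 0.0833)/(0.0588 + 0.0833)) = sqrt(0.1643/0.1422) = 1.075.

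**Step 3: standard error of the within-arm change.** With no unclustered arm to dilute it, the ratio is sqrt(DE), taking the ICC to apply to change scores. At ICC 0.05 it is sqrt(1.376) = 1.17.

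**Step 4: type I error of the tests as planned.** Simulation with normal data, total variance 1 in each arm, true mean difference or mean change zero, and 100,000 runs per ICC.

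| Assumed ICC | DE | Effective n (of 17) | SE ratio, between arms | SE ratio, paired | Type I error, between arms | Type I error, paired |
|---|---|---|---|---|---|---|
| 0 | 1.00 | 17.0 | 1.000 | 1.00 | 4.9% | 5.0% |
| 0.01 | 1.08 | 15.8 | 1.015 | 1.04 | 5.4% | 5.8% |
| 0.05 | 1.38 | 12.4 | 1.075 | 1.17 | 6.8% | 9.2% |
| 0.10 | 1.75 | 9.7 | 1.145 | 1.32 | 8.7% | 13.6% |
| 0.20 | 2.51 | 6.8 | 1.274 | 1.58 | 13.0% | 22.3% |

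Effective n is 17/DE. Repeat simulations differ by about 0.2 percentage points, and the Welch version of the between-arm test behaves almost the same.

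**Step 5: the mixed model.** The grouping unit of its random effects is not named. Their description as initial score and change reads as participant level, and with exactly two random effects specified none remains for cohort. It therefore offers no protection.

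**The case against.** Five points can be made on the other side.

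- **A reader might infer that the standard errors are certainly too small.** The article does not show that. It gives no ICC, part of the weekly dose is an individual module of about one hour, and at ICC 0 there is nothing to correct. This stands: the point is conditional.
- **A reader might infer that randomisation fails to protect the between-arm test in all cases.** It does not follow. If the programme affects nobody, grouping creates no correlation and the individually randomised comparison keeps its level. The between-arm figures apply where group effects are real but average to zero and inference extends to other groups. This stands as a condition on those figures; it does not rescue the paired tests, which have no randomised comparison behind them.
- **A reader might infer that facilitators or calendar period differed between cohorts.** The article says only that two trained team members cofacilitate. It does not say whether the same pair led both cohorts, or whether the cohorts ran together or in turn. Those sources of correlation are undocumented. Interaction within the group is documented, and it is enough to raise the question.
- **The feedback questionnaire.** Its between-arm t test also lacks a cohort term, but controls later received the programme and their grouping is not described. The one-arm design effect above may not fit that test.
- **This is a pilot, and a condensed article may leave such detail to an analysis plan.** The pilot status limits the consequences, and at ICC 0.01 to 0.05 the between-arm effect is modest. But the article does not leave the analysis open: it names the tests, counts the model terms and fixes the threshold, and that specification does not match the delivery it reports.

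**Conclusion.** The concern holds in conditional form. The treated arm was formed into two interacting groups, no listed analysis allows for correlation within them, and any positive ICC makes standard errors involving that arm too small. Over assumed ICCs of 0.01 to 0.20, the understatement means that correct intervals would be 1.5% to 27% wider between arms and 4% to 58% wider within the arm. The within-arm figures need the same ICC to hold for change scores. The between-arm type I error figures need group effects that exist but average to zero. The paired tests are the weaker part of the plan on this point; the between-arm test is affected little unless the ICC is near 0.10 or above.

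**What to change.** A random cohort effect is not a workable repair, because two cohorts cannot support an estimate of the cohort variance. Instead, add to Data Analysis Planning:

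1. A sensitivity table for assumed ICCs of 0.01, 0.05, 0.10 and 0.20. Multiply the SE of the between-arm difference by 1.015, 1.075, 1.145 and 1.274, and the SE of the within-arm paired change by 1.04, 1.17, 1.32 and 1.58. State that the ICCs are assumed.
2. Results shown separately for the cohorts of 9 and 8.
3. P values presented as exploratory. No single ICC should serve as a rule for calling a result significant, since nothing in the article supports one value over another.
4. A stated limitation that the intervention effect cannot be separated from influences specific to these two cohorts.

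The cost is a little more analysis and wider intervals, to the extent given above. No new data are needed, and the article reports that analysis was still in progress.
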